##### Trunk impairment

2.2.1.10

The Trunk Impairment Scale (TIS) will be used to evaluate the trunk control of the participants (45). The TIS assesses static and dynamic sitting balance and trunk coordination in a sitting position, generating a total score between 0 and 23, where a higher score indicates better trunk control. Static sitting balance (score range 0–7) evaluates the ability to remain in a seated position with both feet on the floor and with the legs crossed. The dynamic sitting balance subscale (score range 0–10) assesses lateral flexion of the trunk, initiated from the upper and lower part of the trunk. The trunk coordination subscale (score range 0–6) assesses rotation from the shoulder and pelvic girdle in the horizontal plane.

##### Functional independence in daily life

2.2.1.11

We will measure functional independence in daily life based on the Functional Independence Measure (FIM, score range 18–126) upon admission and discharge from the rehabilitation ward. The FIM includes measures of independence for self-care, including sphincter control, transfers, locomotion, communication, and social cognition (46). It is an 18-item, 7-level, ordinal scale intended to be sensitive to changes over the course of a comprehensive inpatient medical rehabilitation program.

##### Cognitive impairments

2.2.1.12

Cognitive impairments will be rated by the Montreal Cognitive Assessment (MoCA) (47), which consists of simple tasks such as drawing, object naming, memory recall, reading, and mathematical operations (0, worst score, 30: best score).

##### Quality of life

2.2.1.13

We will rely on EQ-5D and Stroke Specific Quality of Life (SSQOL) to measure the quality of life after stroke. EQ-5D is a generic quality-of-life measure and it includes mobility, self-care, usual activities, pain/discomfort, and anxiety/depression (48). The SSQOL measures 12 domains including mobility, energy, upper extremity function, work/productivity, mood, self-care, social & family roles, vision, language, thinking, and personality (49).

#### Neurophysiological assessment (for participants with SAFE score <5 and without medical contraindications)

2.2.2

Transcranial magnetic stimulation (TMS) will be applied over the motor cortex to depolarize neurons and lead to motor evoked potentials (MEPs) for assessing the cortico-spinal excitability as well as resting motor threshold values (RMT) (50). MEPs are the electrical signals recorded from muscles following stimulation of motor pathways within the brain. Surface electromyography (EMG) electrodes are attached to the extensor carpi radialis (ECR) and first dorsal interosseous (FDI) for EMG recording. The “hot spot” of the MEP from ECR and FDI will be first identified in the contralesional (less affected) hemisphere, followed by the ipsilesional (more affected) hemisphere. TMS will be carried out using MagPro R30 (MagVenture, Inc., Denmark).

The main outcome measure of the TMS assessment is a patient’s MEP status, i.e., whether or not MEPs with consistent latencies can be evoked from the ipsilesional hemisphere.

Participants will be considered MEP positive if MEP of any amplitude but with consistent latency can be elicited while the ECR/FDI muscle is either at rest or is preactivated. If this criterion is not met even when stimuli are delivered at maximal intensity, the participant will be considered MEP negative.

For participants who are unable to achieve a RMT, an active motor threshold will be examined. The participant will perform an active wrist extension/make a fist with the less affected hand and hold it there during stimulation, while the investigator looks for a MEP in the ECR or FDI. For active motor threshold, the participant will be considered MEP positive if any amplitude of consistent latency can be elicited in 50% of at least 8 trials while the muscle is active.

Inspired by the PREP2 algorithm (36, 38), TMS measurements will only be formed at T0 and for patients with SAFE scores less than five. This may aid in the understanding of subgroups with good, limited, and poor recovery potential.

#### Technology-assisted assessment

2.2.3

##### Virtual Peg Insertion Test (VPIT)

2.2.3.1

The VPIT is a technology-assisted assessment that provides 10 sensitive and validated metrics describing upper limb movement patterns and hand grip forces (21, 22, 51, 52) (Figure 1). The VPIT consists of a virtual goal-directed pick-and-place task that requires coordinated arm and hand movements. It allows for gathering 3D upper limb endpoint kinematic and kinetic data in persons with mild to moderate upper limb impairments. The participant is instructed to squeeze and hold a commercial haptic device to pick up a peg and then insert it into one of the holes on the other side of the virtual board by releasing the force on the handle. The collected raw kinematic and kinetic data is transformed through a signal processing framework into 10 sensor-based digital biomarkers that provide information on different aspects of task performance, including for example movement smoothness, accuracy, and speed (21). These digital biomarkers and their clinimetric properties were previously validated in different neurological population (21, 22, 53). The data provide an objective, robust, and clinically feasible way to assess functionally relevant sensorimotor impairments in the arm and hand in chronic post-stroke individuals with mild to moderate sensorimotor deficits.

**Figure 1 fig1:**
[figure not shown]
Technology-assisted assessments used in this study. Virtual Peg Insertion Test (VPIT, top), ETH MIKE (middle), and ZurichMove sensors (bottom).

##### ETH motor impairment and kinesthetic evaluation (MIKE)

2.2.3.2

The ETH MIKE is a one-degree-of-freedom end-effector device, that can be used to measure impairment of proprioception, motor and sensorimotor function in the metacarpophalangeal joint of the index finger (23, 54, 55). The ETH MIKE provides well-controlled stimuli to the index finger and sensitively measures the kinematic and kinetic responses, and has been shown to be safe and feasible in post-stroke individuals with mild to severe disability levels (23). Specifically, there is one task for proprioception assessment (gauge position matching (56)), with the absolute position matching error as the main outcome measure. Further, there are three tasks focused on motor impairments (active and passive range of motion, maximum force generation, and fast target reaching), providing as main outcomes active and passive range of motion, maximum finger force, and maximum movement speed for both flexion and extension. Additionally, one task is designed to evaluate the ability to integrate proprioceptive information during the execution of a complex movement, i.e., to assess sensorimotor impairments (trajectory following), providing the root means square tracking error as the main outcome measure. Thus, ETH MIKE is able to provide sensitive and objective measures of proprioception, motor impairments, and sensorimotor impairments that could inform the evolution of somatosensory and sensorimotor functions during recovery. Similar to the VPIT, the digital biomarkers used as outcome measures for the ETH MIKE were previously validated in different neurological population (23, 57, 58).

##### ZurichMove

2.2.3.3

The ZurichMove sensors are custom-made wearable sensors developed by ETH Zurich (59) that allow unobtrusively monitoring the usage of the upper limb in the context of daily life activities.^1^ These sensors incorporate a 3-axis accelerometer, a 3-axis gyroscope and a 3-axis magnetometer. They can continuously record for approximately 3 days with a sampling frequency of 50 Hz. In this study, participants have to wear 5 ZurichMove sensors on both wrists, ankles and chest continuously for 48 h while performing all normal daily activities (in the clinic or at home for later time points). These sensors are attached to the body with non-gripping elastic bands by research staff or a caregiver and can be removed for showers and re-strapped by caregivers. Participants will record activities performed during the 48 h of wearing the sensors in a diary. Previously, the safety and usability of the wearable sensors have been established and the following outcome measures were defined and validated (60, 61). We aim to extract the duration of arms use in the clinical setting and during daily living by computing metrics such as upper limb activity counts as an approximation for the amount of limb usage (62), the gross movement score with an aim to identify functional relevant activities (60) and the GMAC (a fusion of both activity count and gross movement score) (63). The laterality ratio can be derived from these metrics to compare activity levels from both arms (64). These wearable sensors will provide digital biomarkers reflecting the usage of the more versus less affected upper limb in daily life.

#### Psychosocial questionnaires and qualitative interviews

2.2.4

We will rely on repeated standardized questionnaires and qualitative interviews conducted in English, Mandarin, and Malay, in order to gain knowledge about the perspectives of individuals with stroke at 6, 12, and 24 months post-stroke. We will not conduct interviews at 3 months post-stroke as some stroke survivors may have not returned to the community in the Singaporean healthcare system. We also will not conduct interviews at 36 months post-stroke as the post-stroke experience may not have significantly changed after 2 years since stroke onset. The main aim is to explore stroke survivors’ experiences in the community qualitatively and quantitatively. Questions related to qualitative interviews focus on participants’ perception related to identity, impairments and the rehabilitation journey (see Supplementary Material). Additionally, we will delve into their perspectives on mental health, spirituality and social support with the following questionnaires: Beck Depression Inventory (65), Generalized Anxiety Disorder Scale (66), Modified Fatigue Impact Scale (67), Insomnia Severity Index (68), Social Support Survey (69), Life Balance Inventory (70) and Mindful Attention Awareness Scale (71). With regards to sample size calculation, guidelines recommended for qualitative samples have been relatively small, ranging from 20–40, to account for the complexity of the analysis. Given the longitudinal nature, the qualitative component of the study will include 30 participants or fewer, if data saturation is reached earlier, with sufficient cognitive function and willingness to share experiences coping with stroke. Interviews will be recorded and transcribed verbatim followed by thematic analyses.

#### Data collection and management

2.2.5

Data from standardized clinical assessments will be collected by TTSH therapists and will be stored on the National Healthcare Group (NHG) REDcap platform electronically. Technology-assisted and neurophysiological outcomes will be collected by TTSH therapists and/or researchers from the Future Health Technologies (FHT) Programme and will be stored on the FHT data infrastructure SECure. Qualitative interviews will be conducted by researchers from the Rehabilitation Research Institute of Singapore, Nanyang Technological University (NTU).

Participants who withdraw from the study will not be replaced. All collected data will be used for analysis. We will also maintain contact with participants between time points to minimize the number of dropouts. In case of missing data, we will consider using controlled multiple imputation (72) to handle the missing data. Controlled multiple imputation is based on the assumption of missing at random and can be used as sensitivity analysis to evaluate the impact of missing data. Missing data will first be imputed following the Bayesian paradigm under the assumption of ignorability (i.e., missing at random). Each imputed dataset will then be analyzed using the substantive analysis model of interest. Finally, Rubin’s rules (73) are applied to give a single multiple imputation estimate for inference.

Regarding the data sharing plan, pseudonymized data will be shared in an access-controlled manner between research teams on a biweekly basis. Only anonymized or aggregated data will be shared with the general public such as researchers from other institutes or government agencies upon reasonable request.

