As the nature of this study is explorative and as there is no generally accepted approach to estimate the sample size requirements for multivariate regression models (29), a classical sample size estimation was not possible. Instead, our target sample was based on previous studies aiming at understanding post-stroke upper limb recovery and logistical considerations. Existing studies have typically reported longitudinal data in samples between 150 to 450 participants (10, 11). Based on this benchmark and considering the annual number of stroke survivors referred to the TTSH inpatient stroke rehabilitation unit as well as a 20% rate of dropout or loss to follow-up, we targeted to enroll 400 participants in the study.

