#### Statistical analysis

2.2.6

To understand post-stroke upper limb impairments and recovery, we will perform descriptive analyses for each outcome measure and various time points. Next, we will explore how different domains are interrelated and how the addition of digital biomarkers can inform key aspects of motor recovery and its dynamics using correlation matrices. We will investigate the relationship between movement quality (e.g., smoothness) and motor recovery, the relationship between somatosensory impairment and motor recovery, the relationship between upper limb use in activities of daily living and motor/somatosensory recovery, and whether these aspects present different time courses, or interact with each other.

To characterize upper limb recovery after stroke longitudinally, we will construct separate statistical models (e.g., mixed-effects models) that characterize the time course of upper limb impairments (FMA-UE) (3), activity capacity (ARAT) (4), activity performance (outcomes of wearable sensors), and quality of life (EQ-5D) post-stroke. We will then construct multivariate mixed models, leveraging on the uniqueness of the rich data set to probe the interaction and interdependence between various outcome measures and identify key determinants of recovery.

A mixture model based on a Bayesian approach (3), a clustering or subgroup identification analysis (74, 75) will then be used to identify subgroups of patients that exhibit distinct, clinically relevant recovery patterns based on a specific subset of variables identified in the above explorative analyses and their dynamics.

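### The missing-data paragraph describes controlled multiple imputation as resting on missing at random and gives no departure step, so followed as written it cannot test the effect of non-random dropout

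*Protocol article*

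**What the plan says.** Section 2.2.5 (Data collection and management) opens tentatively: "In case of missing data, we will consider using controlled multiple imputation". It then characterises the method: "Controlled multiple imputation is based on the assumption of missing at random and can be used as sensitivity analysis", the purpose being to gauge the impact of missing data.

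Three steps follow:

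1. "Missing data will first be imputed following the Bayesian paradigm under the assumption of ignorability (i.e., missing at random").
2. "Each imputed dataset will then be analyzed using the substantive analysis model of interest".
3. Rubin's rules, introduced as the final step, "are applied to give a single multiple imputation estimate for inference".

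Section 2.2.6 (Statistical analysis) plans separate longitudinal models for FMA-UE, ARAT, wearable-sensor outcomes and EQ-5D, with mixed-effects models as the example. Multivariate mixed models come next, then a mixture, clustering or subgroup analysis.

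Section 2.1 sets the enrolment target of 400 from earlier studies, referral numbers "as well as a 20% rate of dropout or loss to follow-up". Table 1 runs to 3 years post-stroke. No other missing-data analysis appears in the article.

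**The concern.** Controlled multiple imputation normally means imputing under MAR and then altering the imputed values in a stated way, for example by a fixed shift, to see how far the conclusion depends on MAR. The article says that the method is based on MAR and lists no step that departs from it. A sensitivity analysis that keeps the assumption in question cannot test that assumption.

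This matters most at the late visits. After discharge, participants are invited back to a hospital clinic for assessments up to 3 years post-stroke, and the Discussion gives long follow-up as a strength of the study. If those who stop attending differ from what their earlier data predict, late trajectories will be biased. A reader could then take the stated analysis as reassurance on a question that it did not address.

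**Working it through.** **1. Does any listed step leave MAR?**

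| Step in Section 2.2.5 | Assumption about unseen values |
|---|---|
| Bayesian imputation under ignorability | MAR |
| Substantive model on each completed dataset | none added |
| Rubin's rules | none added |

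No step shifts the imputed values or models a not-at-random mechanism. The word first, attached to the imputation step, could hint at a later departure, but the next steps are analysis and pooling.

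**2. What do the main models assume?** The article does not say. Likelihood-based mixed models fitted to all observed data are valid under MAR. This is general theory, applied to the example in Section 2.2.6.

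**3. Size of what goes untested.** Inputs from the document: N = 400 and 20% loss.

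- Retained: 400 × (1 − 0.20) = 320. Lost: 400 − 320 = 80. The target of 400 was not derived from a formula, so there is no power figure to reproduce.
- Movement in a visit mean = missing fraction × departure of the unseen values from their MAR prediction.
- Departure of 2 points (assumed): 0.20 × 2 = 0.4 FMA-UE points.
- Departure of 5 points (assumed): 0.20 × 5 = 1.0.
- Departure of 10 points (assumed): 0.20 × 10 = 2.0.
- For scale, the 95% CI half-width with an assumed SD of 20 is 1.96 × 20/√320 = 2.19 points.

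If the unseen values lie below prediction, the MAR mean is too high by these amounts. If they lie above, it is too low.

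**4. Illustration without other variables.** Assumed: 300 runs, N = 400, two visits of one outcome, SD 15, correlation 0.85, about 20% missing, and dropout dependent on the part of the unseen score that the earlier visit does not predict.

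| Estimate of the late mean | Value |
|---|---|
| Full data | 44.92 |
| Likelihood (mixed model) | 46.26 |
| MAR multiple imputation | 46.26 |
| Imputation with a shift of −5 | 45.25 |

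Both MAR methods are off by 46.26 − 44.92 ≈ 1.3 points and agree with each other. Only the shifted analysis moves the estimate: 46.26 − 45.25 ≈ 1.0, which is about 0.20 × 5.

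**5. Illustration with another measured variable.** The same N, SD, correlation and missing share, but dropout depends on a second measured variable.

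| Estimate of the late mean | Value |
|---|---|
| True mean | 45.0 |
| Complete cases | 47.2 |
| Likelihood, FMA-UE only | 46.0 |
| MAR imputation including the second variable | 45.0 |

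Here MAR imputation differs from the single-outcome model by 46.0 − 45.0 = 1.0 point, and usefully so. The gain comes from making MAR more plausible, not from examining a departure from it.

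**The case against.** **MAR imputation is not redundant.** A reader might infer that the imputation will agree with the main result whatever the truth. The documents do not support that. The battery is multimodal and the first models are separate by outcome, so imputation that draws on other measured variables can shift the estimate, as step 5 shows. It also serves missing covariates, the descriptive analyses and the correlation matrices, where no mixed model is being duplicated. What remains is narrower: it does not probe not-at-random dropout.

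**The text is tentative and condensed.** The method is only to be considered, mixed models are an example, and no split between main and sensitivity analysis is fixed. The article names controlled imputation and cites a source for it. The size of shifts and the tipping-point rule can properly sit in an analysis plan that is not shown. This stands as to detail. It does not rescue the sentence, which states the wrong assumption for the method, followed by a sequence that closes with pooling.

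**Pooling of subgroups.** Because Section 2.2.6 says that a mixture or clustering analysis "will then be used to identify subgroups of patients that exhibit distinct, clinically relevant recovery patterns", a reader might infer that class labels will be pooled by Rubin's rules. The article nowhere says so, and a Bayesian mixture model, the first option listed, can be fitted directly to the observed longitudinal data. That criticism should not be made.

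**Direction of bias.** A reader might infer that 3-year results will look too good because those who decline stop attending. That is plausible but not documented; well-recovered participants may also stop. The three research questions in the Introduction concern the added value of digital biomarkers, interdependence between domains and determinants of recovery, not a 3-year mean as such.

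**Conclusion.** The concern holds in a limited form. Section 2.2.5 misdescribes controlled multiple imputation, and the procedure as listed is MAR imputation throughout. Followed as written, it leaves the effect of non-random dropout unexamined in a cohort that expects 20% loss over follow-up of up to 3 years.

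The untested movement in a late-visit mean is 0.20 times the departure from MAR: 1 to 2 FMA-UE points for an assumed departure of 5 to 10 points. That is below the 2.19-point half-width obtained with an assumed SD of 20, though a larger sample would not remove it. The departure, the SD and the direction are all assumptions. That the main models rest on MAR is inferred from the mixed-model example.

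The study is exploratory, makes no power claim and does not commit firmly to the method. The point should be fixed, but it does not threaten the validity of the study as a whole.

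**What to change.** 1. Reword the description in Section 2.2.5 to say that controlled multiple imputation imputes under MAR and then applies explicit departures from it.
2. Add the missing step after the MAR imputation: delta-adjusted or pattern-mixture imputation over a stated range for the late-visit outcomes (FMA-UE, ARAT, EQ-5D and wearable-sensor arm use). Apply shifts in both directions, since the direction of any bias is unknown. Report the tipping point at which a conclusion changes.
3. Keep MAR imputation or likelihood-based mixed models as the main handling of missing data, and state which it is.

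The cost is revised wording, a few extra analysis runs and the need to choose and justify a range of shifts for each outcome. No additional assessments are needed.

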#### Statistical analysis

2.2.6

To understand post-stroke upper limb impairments and recovery, we will perform descriptive analyses for each outcome measure and various time points. Next, we will explore how different domains are interrelated and how the addition of digital biomarkers can inform key aspects of motor recovery and its dynamics using correlation matrices. We will investigate the relationship between movement quality (e.g., smoothness) and motor recovery, the relationship between somatosensory impairment and motor recovery, the relationship between upper limb use in activities of daily living and motor/somatosensory recovery, and whether these aspects present different time courses, or interact with each other.

To characterize upper limb recovery after stroke longitudinally, we will construct separate statistical models (e.g., mixed-effects models) that characterize the time course of upper limb impairments (FMA-UE) (3), activity capacity (ARAT) (4), activity performance (outcomes of wearable sensors), and quality of life (EQ-5D) post-stroke. We will then construct multivariate mixed models, leveraging on the uniqueness of the rich data set to probe the interaction and interdependence between various outcome measures and identify key determinants of recovery.

A mixture model based on a Bayesian approach (3), a clustering or subgroup identification analysis (74, 75) will then be used to identify subgroups of patients that exhibit distinct, clinically relevant recovery patterns based on a specific subset of variables identified in the above explorative analyses and their dynamics.

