**Statistics:**

Descriptive analyses will be first performed to understand post-stroke upper limb impairments and recovery at various time points. The relationships between digital biomarkers and various domains will be explored to inform key aspects of upper limb recovery and its dynamics using correlation matrices. Multiple statistical models will be constructed to characterize the time course of upper limb recovery post-stroke. Subgroups of stroke survivors exhibiting distinct recovery profiles will be identified.

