## Introduction

1

At least 50% of stroke survivors suffer from upper limb impairments in the acute stage (1, 2), and the variety of recovery profiles widely vary (3, 4). Gaining a better understanding of the neurophysiological, behavioral and contextual factors affecting recovery post-stroke is essential to developing more tailored and optimized upper limb rehabilitation approaches and reducing the risk of persistent upper limb impairments (5, 6), which are known to lead to poor self-efficacy (7) and low self-reported health-related quality of life (Hr-QOL) (8, 9). However, this relies on rich data sets tracking upper limb sensorimotor recovery with sufficient time resolution and for a sufficiently long time beyond the initial hospitalization, and considering the multi-dimensional nature of upper limb deficits and their impact on quality of life.

During the last few years, understanding the time course of recovery after stroke as well as its major determinants has received increasing attention (10–14). However, only few data sets have collected information (i) with a high temporal resolution (i.e., multiple time points during both acute/subacute and chronic phases), (ii) over a time period longer than 1 year [but see (14, 15)], (iii) in a large and representative patient sample, and (iv) through the lens of multiple domains of functioning, Hr-QOL and disability. First available data sets, particularly measuring the recovery of upper limb function (3, 4, 16, 17), have revealed important new insights into predicting rehabilitation outcomes (3, 16) and, recently, also trajectories of recovery (4). Here, we aim to investigate the added value of technology-assisted assessments in an Asian cohort longitudinally. “Digital biomarkers,” i.e., metrics derived from technology-assisted assessments (18–20), offer the advantage of providing validated (21–23), objective and traceable descriptions of upper limb behavior on sensitive, continuous scales, often without ceiling effects (24). Digital biomarkers are helpful to complement clinical scores, uniquely inform on movement quality and allow for separating behavioral restitution from compensatory strategies (25), a key aspect that existing longitudinal studies on recovery failed to capture (10, 13).

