To reach this aim, we designed a study protocol to gather a rich multimodal data set tracking the time course of upper limb recovery in a representative cohort of 400 Asian adults after ischemic or hemorrhagic stroke for up to 3 years and characterize the longitudinal relationship between upper limb recovery and independence/quality of life of post-stroke individuals. Compared to Caucasian stroke survivors, Asian stroke survivors have a higher incidence of intracerebral hemorrhages (ICH), lacunar ischemic strokes (IS) and strokes in the young (<45 years) as well as differential recovery patterns between ICH and IS strokes (26–28). However, there is scarce evidence on the profiles of the Asian stroke population. To answer this, we will employ a carefully selected battery of standardized clinical tests, technology-assisted assessments, neurophysiological assessments, tools for measuring Hr-QOL, as well as qualitative interviews with longitudinal follow-ups to uncover different recovery profiles in Asian stroke survivors. Our data set will, thus, assess multiple domains of upper limb recovery with a focus on sensorimotor function.

Such a longitudinal, comprehensive data set will yield clinically important information on key factors influencing post-stroke upper limb sensorimotor recovery trajectory, activity capacity, activity performance, real-world participation, and quality of life over time. We will use this data set to answer the following research questions: (i) Can digital biomarkers revealed by technology-based assessments and wearables deepen our understanding of post-stroke upper limb recovery when compared to neurophysiological measurements (transcranial magnetic stimulation, TMS), standardized clinical assessments, patient self-reports, and Hr-QOL? (ii) What is the interaction and interdependence between sensorimotor impairments, clinically assessed performance, neurophysiology, quality of life, and upper limb usage in daily life, for stroke survivors? (iii) What are the major determinants of recovery? This data set will provide a new means for quantifying the “natural course” of post-stroke recovery in accordance with the standard of care, providing a strong data-driven foundation on which future therapy could be potentially optimized.

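### Added value of digital biomarkers is a stated aim, but the only method tied to it is correlation matrices, which do not by themselves measure gain over clinical scores

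*Protocol article*

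**What the plan says.** The Introduction (section 1) states the purpose: "we aim to investigate the added value of technology-assisted assessments in an Asian cohort longitudinally". Research question (i), in the same section, asks: "Can digital biomarkers revealed by technology-based assessments and wearables deepen our understanding of post-stroke upper limb recovery when compared to neurophysiological measurements", and goes on to list clinical assessments, self-reports and health-related quality of life as further comparators.

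Section 2.2.6 (Statistical analysis) names the tool. After descriptive analyses, the authors will explore how domains are related and "how the addition of digital biomarkers can inform key aspects of motor recovery and its dynamics using correlation matrices". The Abstract, under Statistics, agrees: "The relationships between digital biomarkers and various domains will be explored to inform key aspects of upper limb recovery and its dynamics using correlation matrices".

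Section 2.2.6 then lists relations to investigate, such as movement quality with motor recovery, without naming a further method for them. Three modelling steps follow:

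- Separate longitudinal models for FMA-UE, ARAT, "activity performance (outcomes of wearable sensors), and quality of life (EQ-5D) post-stroke".
- A joint step across outcomes: "We will then construct multivariate mixed models, leveraging on the uniqueness of the rich data set to probe the interaction and interdependence between various outcome" (the sentence continues). This step is also to find the determinants of recovery.
- A subgroup analysis on variables picked out by the preceding exploratory work.

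**The concern.** Added value is a conditional idea: what a digital metric tells once FMA-UE, ARAT, the sensory assessment and, where measured, MEP status are known. A single correlation is marginal. A high correlation between a VPIT metric and FMA-UE may mean that the metric is redundant. A low one may mean new information, or only noise. Neither reading is settled by the coefficient.

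The authors know the difference. The Discussion (section 3) raises, for MEP status, the debate on whether it improves prediction beyond clinical tests. No such comparison is stated for the digital biomarkers, which the Discussion lists first among the study's unique features.

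At stake is how the aim gets answered. The same table of correlations could be read as supporting or denying added value. Because the subgroup analysis draws its variables from the exploratory steps, redundant metrics could also pass into the recovery profiles.

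**Working it through.** The article gives no figure to reproduce. The target of 400 has no formula behind it (section 2.1), and no correlation, effect size or significance level is stated. The check has two parts.

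**1. Which method is assigned to which task (section 2.2.6)**

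| Step | Stated task | Digital metrics named | With-versus-without comparison stated? |
|---|---|---|---|
| Correlation matrices | What adding digital biomarkers can inform | Digital biomarkers in general | No |
| Separate longitudinal models | Time course of each outcome | Wearable outcomes only, as an outcome | No |
| Multivariate mixed models | Interdependence of outcomes; determinants of recovery | None | No |
| Mixture, clustering or subgroup analysis | Distinct recovery patterns | None | No |

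The tasks of the multivariate mixed models match research questions (ii) and (iii). Only the first row is linked in words to the contribution of the biomarkers.

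**2. Whether a pairwise correlation fixes the gain**

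Let y be a recovery outcome, c a clinical score and d a digital biomarker. In a linear model with two predictors:

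- Added R² = (r_yc² + r_yd² − 2·r_yc·r_yd·r_cd) / (1 − r_cd²) − r_yc²
- Partial correlation of d with y given c = (r_yd − r_yc·r_cd) / √[(1 − r_yc²)(1 − r_cd²)]

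Assumed for illustration: r_yc = 0.75 and r_yd = 0.60, both held fixed. Then r_yc² = 0.5625, r_yd² = 0.36 and their sum is 0.9225. Only the overlap r_cd varies.

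| r_cd | R² with both predictors | Added R² | Partial correlation |
|---|---|---|---|
| 0.90 | (0.9225 − 0.81)/0.19 = 0.592 | 0.030 | −0.26 |
| 0.80 | (0.9225 − 0.72)/0.36 = 0.5625 | 0.000 | 0.00 |
| 0.60 | (0.9225 − 0.54)/0.64 = 0.598 | 0.035 | 0.28 |
| 0.40 | (0.9225 − 0.36)/0.84 = 0.670 | 0.107 | 0.49 |
| 0.30 | (0.9225 − 0.27)/0.91 = 0.717 | 0.155 | 0.59 |

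The biomarker-outcome entry is 0.60 in every row, yet the added R² runs from 0.000 to 0.155. The relation is not even monotone: at an overlap of 0.90 the metric adds a little again, with the opposite sign. A pairwise entry read alone therefore says nothing definite about added value.

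**The case against.** The strongest reply is that section 2.2.6 does not stop at correlations. The multivariate mixed models could include biomarkers alongside clinical scores and so give an adjusted answer. This stands. A reader might infer that the study cannot answer its central question, and the article does not support that. The data and a suitable class of model are both there, added value belongs to one of three research questions, and none is labelled central. What remains is that the text does not give these models this task.

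Second, a full correlation matrix at one visit does determine partial correlations and added R² in a linear model, as the working uses. This stands too, so it would be wrong to say that a matrix can never show added value. But the article does not state that further step. A single-visit matrix would also not handle repeated measures, or the ordinal, ceiling-limited scores that the Discussion describes.

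Third, question (i) asks about deeper understanding. Much of the case for the biomarkers concerns measurement properties: continuous scales, movement quality, and telling restitution from compensation. The Discussion leaves prediction models to later work. This stands in part: incremental prediction is not the whole of question (i). The Introduction's added-value aim still needs a quantity.

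Fourth, this is a condensed article of an exploratory study, and covariates or cross-validation may sit in a fuller document. Their absence is no finding. The point is that the one method the article does name for this purpose does not measure it.

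A reader might also count the entries of such a matrix and predict a number of chance findings. The article states no significance test or level for the matrices, and a null of no relation is implausible among measures of the same impaired arm. The point does not rest on that count.

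**Conclusion.** The concern holds in a limited form. The added-value aim is tied by name only to correlation matrices, and pairwise correlations do not by themselves measure what VPIT, ETH MIKE and ZurichMove metrics tell beyond clinical scores. The later multivariate mixed models could fill the gap but are not assigned to it, and VPIT and ETH MIKE metrics are named in no model.

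The size can only be illustrated. With correlations of 0.60 and 0.75 with the outcome, the added R² is 0.000 to 0.155 for overlaps of 0.80 down to 0.30. These inputs are assumptions, the model is linear with two predictors, and other values would give another range. The qualitative result does not depend on them: the gain depends on the overlap, which the biomarker-outcome correlation does not show.

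This should be changed, because a concrete comparison on data already scheduled would answer the study's own aim. It is not a flaw in the design or the data collection.

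**What to change.** In section 2.2.6, keep the correlation matrices as descriptive, shown as estimates with intervals. Then state that the added-value part of question (i) is addressed by nested models with and without the digital biomarkers:

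- **Outcomes:** for example ARAT and EQ-5D at T4 and T5.
- **Base model:** age, days since stroke, and T0 FMA-UE, ARAT, sensory assessment (NSA) and MoCA. Table 1 schedules all four scores at T0. EQ-5D starts at T2, so its models have no T0 value of the outcome.
- **Extended model:** the base model plus the T0 VPIT, ETH MIKE and ZurichMove metrics, with shrinkage because they are many and overlapping.
- **Reported quantity:** the change in cross-validated R-squared or prediction error, with its interval.
- **Arm use as an outcome:** laterality of arm use is itself a ZurichMove metric (section 2.2.3.3). If such a metric is the outcome, put its own T0 value in the base model and test only VPIT and ETH MIKE metrics as additions. Otherwise part of the gain is just the outcome's own baseline.
- **VPIT:** section 2.2.3.1 describes it for mild to moderate impairment. Fit these models in participants able to perform the test, and state that restriction.
- **MEP status:** it is measured only at SAFE scores below 5 (section 2.2.2), so treat it as a separate comparison in that subset.

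The cost is wording, programming and more analysis work, with no new assessments. The VPIT models will have a reduced sample. The reported gain may be smaller than the raw correlations suggest.
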